## Abstract

**Background:**

Given the large genetic heterogeneity in amyotrophic lateral sclerosis (ALS), it seems likely that genetic subgroups may benefit differently from treatment. An exploratory meta-analysis identified that patients homozygous for the C-allele at SNP rs12608932, a single nucleotide polymorphism in the gene *UNC13A*, had a statistically significant survival benefit when treated with lithium carbonate. We aim to confirm the efficacy of lithium carbonate on the time to death or respiratory insufficiency in patients with ALS homozygous for the C-allele at SNP rs12608932 in *UNC13A*.

**Methods:**

A randomized, group-sequential, event-driven, double-blind, placebo-controlled trial will be conducted in 15 sites across Europe and Australia. Patients will be genotyped for *UNC13A*; those homozygous for the C-allele at SNP rs12608932 will be eligible. Patients must have a diagnosis of ALS according to the revised El Escorial criteria, and a TRICALS risk-profile score between −6.0 and −2.0. An expected number of 1200 patients will be screened in order to enroll a target sample size of 171 patients. Patients will be randomly allocated in a 2:1 ratio to lithium carbonate or matching placebo, and treated for a maximum duration of 24 months. The primary endpoint is the time to death or respiratory insufficiency, whichever occurs first. Key secondary endpoints include functional decline, respiratory function, quality of life, tolerability, and safety. An interim analysis for futility and efficacy will be conducted after the occurrence of 41 events.

**Discussion:**

Lithium carbonate has been proven to be safe and well-tolerated in patients with ALS. Given the favorable safety profile, the potential benefits are considered to outweigh the burden and risks associated with study participation. This study may provide conclusive evidence about the life-prolonging potential of lithium carbonate in a genetic ALS subgroup.

**Trial registration:**

EudraCT number 2020-000579-19. Registered on 29 March 2021.

**Supplementary Information:**

The online version contains supplementary material available at 10.1186/s13063-022-06906-5.

## Introduction

### Background and rationale {6a}

Amyotrophic lateral sclerosis (ALS) is a rare, progressive neurodegenerative disorder leading to muscle weakness, behavioral symptoms, respiratory failure and, ultimately, death within on average three years after symptom onset [1, 2]. Patients with ALS are highly variable in their clinical presentation and progression rate, with survival times varying from a few months to over twenty years. The survival time after diagnosis is, on average, 17.7 months (95% CI 17.0–18.4) [3]. The lifetime risk of ALS is 1 in 300, with men being more susceptible than women, while prevalence remains limited with 3 to 5 cases per 100,000 people due to its poor prognosis [2, 4].

Riluzole, a glutamate release inhibitor, is currently the only licensed drug in Europe and extends the life expectancy by a few months [5]. Many different compounds have been investigated in order to expand the therapeutic options, but clinical trials have been mostly futile due to a variety of reasons [6, 7]. Over the last decade, it has become increasingly evident that ALS may not be a single disease, but could be considered a collection of disorders with clinically similar phenotypes yet variable underlying pathophysiological pathways and genetic mutations [1].

It seems unlikely, therefore, that we will be able to treat all forms of ALS with the same single drug. The heterogeneity in treatment response was confirmed in an exploratory meta-analysis of 606 patients treated with lithium carbonate [8]. Overall, no benefit to survival was observed in the general ALS population, but a subgroup of patients homozygous for the C-allele at SNP rs12608932 in *UNC13A* seemed to benefit of lithium carbonate. Lithium carbonate is an approved drug which is used extensively in the treatment of psychiatric illnesses, such as bipolar disorder, depression and psychosis [9–11]. It has been shown to influence many pathways, including the induction of sprouting of pyramidal neurons in the corticospinal tract and the promotion of synaptogenesis, and plays a role in autophagy [12]. All these mechanisms are potentially relevant to ALS, whereas the *UNC13A* protein is involved in synaptic vesicle maturation and neuronal outgrowth [13].

In this study, we aim to validate the exploratory findings of the meta-analysis and confirm the potential of lithium carbonate to prolong the time to death or respiratory insufficiency in patients with ALS homozygous for the C-allele at SNP rs12608932 in *UNC13A.* We will initiate a group-sequential, placebo-controlled, event-driven design to generate confirmatory evidence and minimize the exposure of patients to potentially ineffective treatment arms. In previous controlled clinical trials, lithium carbonate was relatively well tolerated with a mild safety profile [14, 15].

### Objectives {7}

The primary objective of this study is to assess the efficacy of lithium carbonate versus placebo on the composite endpoint of respiratory support free survival, defined as death from any cause or respiratory insufficiency in patients with ALS.

Secondary objectives of this study include the effect of lithium carbonate versus placebo on a combined assessment of mortality and measures of daily functioning, the revised Amyotrophic Lateral Sclerosis Functional Rating Scale (ALSFRS-R), respiratory function, plasma creatinine, and the time to reach advanced disease stages. Further secondary objectives are to evaluate the safety and tolerability of lithium administered orally to patients with ALS, and to assess the effect of lithium carbonate versus placebo on change in urinary P75^ECD^, in plasma neurofilament light and heavy chain, on cognitive functioning and on quality of life.

### Trial design {8}

This is a phase III, event-driven, double-blind, randomized, placebo-controlled, group sequential study to evaluate the efficacy of lithium carbonate in patients with ALS homozygous for the C-allele at SNP rs12608932. Assuming a prevalence of 14.21%, approximately 1200 patients will be genotyped in order to enroll 171 patients. Patients will be randomized to receive either lithium carbonate or placebo in a ratio of 2:1, resulting in 114 patients on lithium carbonate and 57 on placebo. To minimize the burden for patients on placebo, we defined an early stopping rule for both futility and superiority.

## Methods: participants, interventions, and outcomes

### Study setting {9}

This study will be conducted in 14 University Medical Centers in Australia, Spain, the UK, Belgium, Sweden, and The Netherlands. A list of participating centers can be found in the Supplementary material.

### Eligibility criteria {10}

A patient must meet all of the following criteria to be eligible to participate in this study:Age ≥ 18 years at the time of screening.Diagnosis of ALS according to the revised El Escorial criteria (possible, probable- laboratory supported, probable or definite) [16].Capable of providing informed consent and complying with trial procedures, including randomization to sub-studies.TRICALS risk profile > -6.0 and < −2.0**.The use of riluzole will be permitted during the study. Patients taking riluzole must be on a stable dose for at least 30 days prior to the baseline visit or stopped taking riluzole at least 30 days prior to the baseline visit.Women of childbearing potential, i.e., following menarche and until becoming post-menopausal unless permanently sterile, must have a negative pregnancy test at baseline and be non-lactating.Men must agree to practice contraception for the duration of the trial and for at least 3 months after last dose of study drug.Men must not plan to father a child or to provide sperm for donation for the duration of the trial and 3 months after the last dose of study drug.Women must not be able to become pregnant (e.g., post-menopausal (i.e., no menses for 12 months without an alternative medical cause), surgically sterile or using effective birth control methods) for the duration of the study. Effective contraceptives are defined as having a failure rate of less than 1% per year when used consistently and correctly and, when applicable, in accordance with the product label, including: abstinence, hormonal contraception, intrauterine device in place for ≥ 3 months.

** The TRICALS risk profile is estimated using an open-access calculator, and is based on seven clinical disease characteristics [17]. The TRICALS risk profile can be conceptualized as a relative summary of prognostic information and is a predictor of the disease progression rate during follow-up [18]. The risk profile indicates how patients compare to each other (i.e., who is faster or slower progressing than average) without estimating the absolute survival time or probability. It is based on the ENCALS survival model, a cross-validated model to predict the composite endpoint death or respiratory insufficiency based on data of 11,475 patients with ALS [19]. The eligibility window was determined using clinical trial data from six independent trial cohorts comprising 1028 patients with ALS [18]. We searched for the optimal eligibility window that resulted in the most homogenous trial population in terms of ALSFRS-R progression without exceeding an exclusion rate of 25.0%.

A potential patient who meets any of the following criteria will be excluded from participation in this study:Patients heterozygous or homozygous for the A-allele at rs12608932 (*UNC13A*).Safety Laboratory Criteria at baseline:ALT ≥ 5 times upper limit of normal (ULN)AST ≥ 3 times ULNBilirubin ≥ 1.5 times ULNPlasma sodium <120 mmol/LCreatinine clearance < 50 mL / min (Cockcroft-Gault) based on Cystatin C; if not available, eGFR can also be calculated based on creatinine clearance.Platelet concentration of < 100 × 109 per LAbsolute neutrophil count of < 1 × 109 per LHemoglobin < 100 g/L (<6.2 mmol/L)Amylase and lipase ≥ 2 times ULN (suspected pancreatitis)Lactate ≥ 2 times ULN (suspected lactate acidosis)Moderate to severe hepatic impairment according to Child-Pugh classification (Class B or higher; score ≥ 7). Child-Pugh classification is based on bilirubin, albumin, International Normalized Ratio (INR) and presence of encephalopathy or ascites.Participation in any other investigational drug trial or using investigational drug (within 30 days prior to screening).Hypothyroidism unresponsive to thyroid hormone supplementation.Patients using non-invasive ventilation (NIV, ≥22 h per day) or having a tracheostomy.Patients taking edaravone within 30 days prior to screening. Edaravone is approved by the FDA, but remains an investigational product in Europe and Australia.Clinically significant history of unstable or severe cardiac (e.g., congestive heart failure, coronary insufficiency and arrhythmias), oncological, hepatic or renal disease, neuromuscular diseases, significant pulmonary disorder or other medically significant illness.Drug or alcohol abuse.Bipolar disorder, unstable psychiatric illness defined as psychosis or untreated major depression within 90 days of the screening visit. This exclusion criterion is based on a prior psychiatric diagnosis that is unstable as determined by the patient’s treating psychiatrist.Presence of frontotemporal dementia which prevents informed consent.Known allergy or hypersensitivity to lithium, or its excipients, or to the components of the placebo.Brain injury with posttraumatic epilepsy or neurologic deficit, excluding a concussion in the medical history. Brain infarction is an exclusion criterion, a transient ischemic attack is not.Addison disease.Patients with the following co-medication: antipsychotics, digoxin and calcium antagonists, carbamazepine, methyldopa, verapamil and diltiazem.Brugada syndrome or family history of Brugada syndrome.

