#### Demography and baseline characteristics

Continuous variables are expressed as mean and standard deviation for normally distributed variables and median and range for non-normally distributed variables. Categorical variables will be presented as number of cases and percentage. Baseline characteristics will be compared between the placebo and intervention arm without significance testing. Demography will be summarized by allocation arm (active *vs.* placebo) and overall. Missing data will not be imputed unless otherwise specified. The following baseline variables will be calculated:Body mass index = weight (kg)/height^2^ (m)SVC _Predicted_ (L) = Predicted using GLI equation (Age, height, ethnicity, sex)Predicted %SVC = [SVC _Observed_ (L)/SVC _Predicted GLI2012_ (L)]*100% [48]Diagnostic delay (months) = [date diagnosis – date symptom onset]/365.25Symptom duration (months) = [date randomization – date symptom onset]/365.25ΔFRS = [ALSFRS-R _Baseline_ – 48]/symptom duration [49]TRICALS risk category: quintiles of the linear predictor based on the model described in Westeneng et al. [19]. Linear predictor is based on age, diagnostic delay, %SVC _Baseline_, ΔFRS, FTD, site of symptom onset, and El Escorial classification (see also {10} Eligibility criteria).Utrecht stage: Based on the ENCALS model, the median survival time from onset is predicted per patient (in months). Utrecht Stage is defined as symptom duration/median predicted survival time. Staging categories are I = 0–0.25; II = 0.25–0.5; III = 0.5–0.75; and IV = >0.75.

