### Methods for additional analyses (e.g., subgroup analyses) {20b}

Subgroup analyses for the primary endpoint will be carried out separately for two predefined subgroups in the same manner as described in the relevant section.

These subgroups are:Utrecht stage: early vs. late (<0.25 vs. >0.25).Neurofilament light chain: high vs. low.

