### Adverse event reporting and harms {22}

Adverse events will be inquired for during each clinical visit and monitored using the LiSERS questionnaires when commencing the intervention. All adverse events reported spontaneously after the study medication has been provided (i.e., after baseline) by the patient or observed by the investigator or staff will be recorded. Due to an average delay of diagnosis of 1 year in Europe and an average life expectancy of 3 years for patients with ALS, a considerable proportion of the included ALS patients are expected to decease during the 2-year follow-up. These deaths are of natural disease progression and will not be reported as SAEs. All AEs will be followed until they have abated or until a stable situation has been reached. Depending on the event, follow up may require additional tests or medical procedures as indicated, and/or referral to the general physician or a medical specialist.

Expedited reporting of suspected unexpected serious adverse reactions (SUSARs) of immediate concern to patient safety will be done by the sponsor through the web portal EudraVigilance to the IRB; this suffices as notification to the competent authority. The remaining SUSARs will be recorded in an overview list accompanied by a brief report highlighting the main points of concern that will be submitted once every half year to the IRB.

The Sponsor will report expedited all SUSARs to the competent authorities in other member states, according to the requirements of the member states. The expedited reporting will occur not later than 15 days after the sponsor has first knowledge of the adverse reactions.

For fatal or life-threatening cases, the term will be maximal 7 days for a preliminary report with another 8 days for completion of the report. In addition to the expedited reporting of SUSARs, the sponsor will submit, once a year throughout the clinical trial, a safety report to the accredited IRB and competent authorities of the concerned member states.

This safety report consists of: a list of all suspected (unexpected or expected) serious adverse reactions, along with an aggregated summary table of all reported serious adverse reactions, ordered by organ system, per study, and a report concerning the safety of the patients, consisting of a complete safety analysis and an evaluation of the balance between the efficacy and the harmfulness of the medicine under investigation.

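### Diagnostic delay and symptom duration are labelled months but computed in years, so the Utrecht stage as printed is 12 times too small and its early/late split practically collapses

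*Protocol article*

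**What the plan says.** The section Demography and baseline characteristics defines diagnostic delay (onset to diagnosis) and symptom duration (onset to randomization). Both carry the label months, and both are a difference of two dates divided by 365.25.

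Two further variables use symptom duration:

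- ΔFRS is the baseline ALSFRS-R minus "48]/symptom duration". No unit is printed for ΔFRS.
- For staging, "the median survival time from onset is predicted per patient (in months"), and "Utrecht Stage is defined as symptom duration/median predicted survival time". The categories follow: "Staging categories are I = 0–0.25; II = 0.25–0.5; III = 0.5–0.75; and IV = >0.75".

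The same section says of the TRICALS risk category that "Linear predictor is based on age, diagnostic delay", ΔFRS and four other characteristics.

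The Utrecht stage is then used twice more. Methods for additional analyses {20b} names it as one of two predefined subgroups for the primary endpoint: "Utrecht stage: early vs. late (<0.25 vs. >0.25"). Item IV of Efficacy: other study parameters compares the mean time spent in each stage between arms, and includes the Utrecht system.

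For the risk profile used at entry, Eligibility criteria {10} states: "The TRICALS risk profile is estimated using an open-access calculator, and is based on seven clinical disease characteristics".

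**The concern.** A date difference in days divided by 365.25 is a number of years. If the difference were already in months, the divisor would have no meaning. No reading of the printed formula yields the months on the label.

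For a purely descriptive variable this would only mislabel a table. Here symptom duration is the numerator of a ratio whose denominator is expressly in months, and fixed cut-offs are applied to that ratio. Coded as written, the formula would push almost all patients below the lowest cut-off. That affects the subgroup analysis, the time-in-stage comparison and the baseline stage table. Any linear predictor or risk category rebuilt from the printed delay and ΔFRS would also be mis-scaled.

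**Working it through.** **Inputs.** The formulas and cut-offs are those above. For typical times, Adverse event reporting and harms {22} gives "Due to an average delay of diagnosis of 1 year in Europe and an average life expectancy of 3 years for patients with ALS". I use 12 months as an illustrative symptom duration and 36 months as an illustrative predicted median. The ALSFRS-R score of 38 below is an assumption.

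**1. Size of the unit error.** Years = days/365.25. Months = days/(365.25/12) = days/30.4375. The ratio is 365.25/30.4375 = 12. An interval of 365.25 days is 12 months, but the printed formula returns 1.0.

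**2. ΔFRS.** For a score of 38 at 12 months:
- with months: (38 − 48)/12 = −0.83 points per month
- as printed: (38 − 48)/1.0 = −10.0, which is points per year

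At 18 months the values are −10/18 = −0.56 and −10/1.5 = −6.67.

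**3. Utrecht stage.** For 12 months' duration and a 36-month predicted median:
- with months: 12/36 = 0.333, stage II, late
- as printed: 1/36 = 0.028, stage I, early

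**4. What it takes to be late as printed.** Let d be the duration and m the predicted median, both in months. The printed stage is (d/12)/m. It exceeds 0.25 only if d > 0.25 × 12 × m = 3m.

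| Predicted median (months) | Duration needed as printed | Duration needed with months |
|---|---|---|
| 12 | > 36 | > 3 |
| 24 | > 72 | > 6 |
| 36 | > 108 | > 9 |
| 48 | > 144 | > 12 |

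**5. How many patients.** The documents do not give the distribution of the true ratio. Assume it is lognormal with median 1/3 and a log-scale SD between 0.4 and 0.8. Then 64% to 76% of patients are truly late, but only 0% to 0.3% are late under the printed formula. That is 0 to about 0.5 of 171 patients.

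**6. Time in stage.** Take the patient of step 3, follow for 24 months and keep the predicted median fixed (an assumption, since the article does not say how the stage is updated). With months, the ratio runs from 12/36 = 0.333 to 36/36 = 1.0, through stages II, III and IV. As printed, it runs from 0.028 to 3/36 = 0.083 and never leaves stage I.

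**7. If the denominator is also wrong.** Steps 3 to 6 assume a correctly predicted median. If the mis-scaled delay and ΔFRS also entered the survival model, and the predicted median shrank by a factor k, the true ratio needed to be late would be 3/k: 1.5 for k = 2, 1.0 for k = 3 and 0.25 for k = 12. The article gives no model coefficients, so k is unknown.

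**The case against.** The strongest reply is that the intent is plain and this is a slip of the pen. Numerator and denominator are both labelled months, and cut-offs at 0.25, 0.5 and 0.75 make sense only in matching units. The same 365.25 appears in the formula for the primary endpoint, without a unit label and so without contradiction; it may simply have been carried over. A literal coding would put nearly everyone in stage I and would probably be noticed. All of this is fair. It means the code may well be right, but it does not make the printed definition right, and the variable feeds a predefined analysis.

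A reader might infer that the error reaches trial entry, the stratification cut at −4.5 or the covariate of the primary test. The documents do not support that. The entry profile comes from the open-access calculator, and the sentence saying so contains no formula and no error. The primary analysis adjusts for the TRICALS Risk Profile under that same name. What the baseline section defines is a separate risk category in quintiles, and nothing in the article plans to rebuild the continuous covariate from the printed times.

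A reader might also infer that the late subgroup would be empty. That is too strong. Background and rationale {6a} describes survival from a few months to over twenty years, so a few very long durations are possible. If the denominator were also mis-scaled, the split could not be determined from the documents.

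**Conclusion.** The definitions of diagnostic delay and symptom duration are wrong as written, by a factor of exactly 12. ΔFRS comes out 12 times larger in magnitude than a monthly rate. The Utrecht stage comes out 12 times too small, provided the predicted median survival is correct. Under that condition the late group is practically empty, and the subgroup analysis, the Utrecht time-in-stage comparison and the baseline stage table would not do what they are meant to do if coded literally. The factor of 12 and the 3m threshold follow from the printed formulas alone; the percentages in step 5 rest on an assumed distribution. Eligibility, stratification and the primary test are not shown to be affected. The point should be corrected before analysis, but it does not threaten the primary result.

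**What to change.** In Demography and baseline characteristics, divide both date differences by 30.4375 (365.25/12), so that diagnostic delay and symptom duration are in months. State ΔFRS as points per month, and derive ΔFRS and Utrecht stage from the corrected values. Check that the analysis code uses months for these variables and for anything built from them, including the risk category. It would also help to add one sentence confirming that the continuous covariate in the primary test is the calculator value described under Eligibility criteria {10}.

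The cost is a wording correction and, if the code copies the printed formula, one line of derivation code. No patient, visit or sample size changes.
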